### Objectives

The primary objective of this trial is to investigate the effects of a day-structuring exercise programme on BPSD in inpatient hospital dementia care. The promising results of our pilot-study regarding the feasibility and effects of the *exercise-carrousel* on BPSD in hospital old age psychiatry care, led to the following study-hypothesis:*The intervention group, carrying out a 2-day-structuring exercise intervention in addition to treatment as usual (TAU), is hypothesized to show reduced BPSD at follow-up. In contrast, the control group, receiving social stimulation in addition to TAU, is not expected to show such changes.*

In addition to investigating the putative effects of the day-structuring exercise on BPSD, the following secondary-endpoint parameters are investigated: caregiver burden, total dose and frequency of application of antipsychotic and sedative medication, circadian rhythms of motor behaviour, saliva cortisol-levels and brain-derived neurotrophic factor.

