### Sample size

The calculation of the sample size was performed via G*Power 3.1 [23], taking into account following parameters: a medium effect size (d = 0.5) for the primary objectives, the overall effects on BPSD measured by the Alzheimer’s Disease Cooperative Study-Clinical Global Impression of Change (ADCS-CGIC) [24, 25], from our pilot-study; a 1:1 allocation rate; two measurements; non-parametric analysis due to ordinal characteristics of the instruments assessing the primary objective; and an α-error of 0.05 and a power of 0.80 (1-ß-error) according to Cohen [26]. Based on this calculation, each group shall include 53 patients. The enrolment of 130 patients is planned, as a drop-out rate of 25 % is expected based on the experience from the pilot study.

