#### Allocation and concealment of allocation

After enrolment and pre-assessment (T0, Fig. 1), group allocation to the study or control group will be realised via minimisation. An external statistician, who is not part of the study team, will run the group allocation via an online minimisation-tool ‘Qminim’ [27]. Minimisation is a well-approved form of randomisation that minimises group differences in pre-defined characteristics while continuing trial enrolment. In order to achieve the best possible balance between the two study arms, group allocation will be performed according to the following factors: sex (double weighted), age, Mini-Mental Status-Examination (MMSE) [28] and Bayer instrumental Activities of Daily Living (B-ADL) [29]. Due to external enrolment in the trial, central randomisation by a person not involved in the study, and the blinding of all investigators during the whole trial, allocation concealment will be realised in the course of the trial.

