#### Analysis

The patients’ baseline characteristics in both groups will be compared via Chi-square test for categorical data, Wilcoxon rank test for non-parametric or non-normally distributed characteristics and *T*-test for continuous and normally distributed characteristics. Pre-post-outcome analysis within and between the groups will be realised per intention-to-treat analysis for the primary outcome variable via Friedman analysis of variance (ordinal characteristics) and analysis of variance for interval characteristics. The analysis of circadian rhythms in motor behaviour will be conducted according to Witting *et al.* [45] by calculating inter-daily stability, intra-daily variability and relative amplitude. Advanced time series analysis of the patients’ daily activity patterns will be developed in accordance with recent developments by Kirste *et al.* [46]. Analysis of the patients’ characteristics and outcome criteria will be realised using SPSS (version 22) and Matlab (version R2014b).

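### The named analyses leave out the four minimisation factors and use baseline values only as a repeated measure; adjusting for them is a near-free gain in calibration and power, of a size the protocol does not let one fix

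*Protocol article*

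**What the plan says.** The section Allocation and concealment of allocation states that "group allocation will be performed according to the following factors: sex (double weighted), age", and goes on to name MMSE and B-ADL. The stated aim is the best achievable balance between the arms.

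The Analysis section then names the outcome methods: "Friedman analysis of variance (ordinal characteristics) and analysis of variance for interval characteristics", applied as a pre-post analysis within and between groups. It mentions no covariate, and neither does any other section.

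The Sample size section is in the same spirit. It assumes "a medium effect size (d = 0.5) for the primary objectives", "a 1:1 allocation rate" and "non-parametric analysis due to ordinal characteristics of the instruments assessing the primary objective", with "an α-error of 0.05 and a power of 0.80 (1-ß-error) according to Cohen", and concludes that "each group shall include 53 patients". No gain from adjustment is built in.

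The primary outcome is the ADCS-CGIC, a rating of change. NPI and CMAI are secondary outcomes; their measurement at T0 is implied by the pre-post design rather than stated scale by scale.

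**The concern.** Minimisation removes most of the chance imbalance between arms on the factors it controls. A test that ignores those factors still counts their contribution as random error. Where the factors are prognostic, the standard error is then larger than the true sampling variation of the treatment difference. The test rejects less often than its nominal level under the null and gives up power under the alternative. The trial takes the trouble to balance four factors and then names analyses that make no use of the balance.

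There is a second, independent loss of precision. With two arms and two time points, the group-by-time test in a pre-post analysis of variance is the same as comparing change scores. That is generally less precise than regressing the T1 value on arm and the T0 value.

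**Working it through.** **1. The plan's own figure.** Inputs from Sample size: d = 0.5, alpha 0.05, power 0.80, 1:1, non-parametric. For a Wilcoxon-Mann-Whitney (WMW) test with normal parent, the effective size per group is m = n × 3/π, the non-centrality is d × √(m/2), and the degrees of freedom are 2m − 2. At n = 53, m = 50.6 and the non-centrality is 0.5 × √25.3 = 2.52. One-sided power is 0.803, so 53 per group is reproduced. This holds for a one-sided test only: the same test two-sided has power 0.702 at 53 and needs 67. The article does not state sidedness, although its hypothesis is directional (the intervention group "is hypothesized to show reduced BPSD at follow-up"). Both cases are shown below.

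**2. Adjustment, by formula.** Covariates explaining R2 of the variance raise the standardised effect to d/√(1 − R2). At 53 per group:

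- R2 = 10%: 0.5/√0.9 = 0.527; power 0.838 one-sided, 0.747 two-sided.
- R2 = 20%: 0.5/√0.8 = 0.559; power 0.875 one-sided, 0.795 two-sided.

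R2 is assumed throughout, because the article gives none.

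**3. Behaviour after minimisation, by simulation.** The settings were 106 patients, four binary minimisation factors with the first double weighted, and assignment probability 0.8 or 1.0. The outcome depended either on the binary factors or on continuous variables behind them. The unadjusted WMW test was compared with a rank regression on arm and factors. There were 2,500 null trials and 1,500 trials at d = 0.5 per setting (Monte Carlo standard error about 0.4 and 1 percentage points). The cut-points, the assignment probability and the continuous outcome scale are assumptions. Ranges are over the four settings.

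| Assumed R2 | Two-sided type I error, unadjusted | Same, adjusted | Two-sided power, unadjusted / adjusted | One-sided power, unadjusted / adjusted |
|---|---|---|---|---|
| 0 | 4.2–5.7% | 4.3–5.6% | 0.69–0.71 / 0.69–0.71 | 0.79–0.81 / 0.79–0.81 |
| 10% | 3.9–4.8% | 4.8–5.6% | 0.70–0.72 / 0.73–0.76 | 0.81–0.83 / 0.83–0.84 |
| 20% | 3.0–3.8% | 4.9–5.6% | 0.69–0.71 / 0.76–0.79 | 0.80–0.83 / 0.84–0.87 |

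Within settings, the gain at R2 = 10% is about 2 points one-sided and 2 to 4 two-sided. At 20% it is 4 to 5 points one-sided and about 7 two-sided (8 in one setting, within simulation error). A separate simulation with 97 patients and a two-sided t-test agrees: type I error 4.1% and power 0.69 against 0.73 at 10%; 3.0% and 0.71 against 0.78 at 20%.

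**4. Secondary interval outcomes.** With pre and post variance both σ² and correlation r, a change score has variance 2σ²(1 − r), and the T1 value adjusted for T0 has residual variance σ²(1 − r²). The ratio is (1 + r)/2:

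- r = 0.3: 0.91/1.40 = 0.65
- r = 0.5: 0.75/1.00 = 0.75
- r = 0.8: 0.36/0.40 = 0.90

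With unequal standard deviations σ0 (T0) and σ1 (T1), change-score variance minus ANCOVA variance is (σ0 − rσ1)², which is never negative. In large samples ANCOVA therefore does not lose precision. The correlations are illustrative; the article gives none.

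**The case against.** The strongest reply is that a journal article condenses the plan, and a covariate list may sit in an analysis plan that is not shown. This has some force for analysis of variance, where naming no covariates is not a decision against them. It has little for the primary outcome: a Friedman test cannot take covariates, so naming it rules adjustment out. The point concerns a stated method, not a silence.

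Second, the conservatism was shown for WMW and t-tests, not for the named Friedman test. This stands. Friedman compares related measurements and gives no between-group contrast, which is a separate and larger problem. The present point applies to whatever between-group test takes its place.

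Third, nothing in the article shows that sex, age, MMSE and B-ADL explain 10% or 20% of a rating of change. This also stands; at low R2 the effect is small and at zero it vanishes.

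Three stronger readings are tempting, and the documents do not support them:

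- A reader might infer that baseline behaviour is ignored altogether. It is not: for outcomes analysed pre-post, the T0 value enters as the first measurement, though less efficiently than as a covariate.
- A reader might infer that omitting baseline NPI from the primary analysis also makes that test conservative. NPI is not a minimisation factor, so its omission only forgoes possible power.
- A reader might infer that the omission pulls power below the planned 80%. The plan assumed no adjustment. At 53 per group and one-sided, unadjusted power stays at about 0.80 or above, within simulation error.

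Finally, the article does not say which scales count as interval, so the ANCOVA argument covers only those treated that way.

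**Conclusion.** The point holds in a limited form. The four minimisation factors are absent from the named analyses. To the extent that they are prognostic, an unadjusted between-group test is conservative and less powerful than an adjusted one. The loss runs from nothing at R2 = 0 to about 4 to 7 power points at an assumed 20%, with two-sided type I error falling to about 3 to 4%. For interval secondary outcomes, a change-score analysis has 1/0.90 to 1/0.65 times the variance of ANCOVA for r between 0.8 and 0.3, assuming equal variances.

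This is a free improvement and not an error that biases the result: the unadjusted comparison remains unbiased and its type I error is not inflated. Any shortfall against 80% power has other sources. One is sidedness (53 against 67 per group). The other is drop-out: 130 × 0.75 = 97.5 completers against 106 required. Adjustment might recover some of that shortfall; leaving it out did not create it.

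**What to change.** Amend the Analysis section before outcome data are seen by arm:

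- **Primary.** Analyse the T1 ADCS-CGIC with a between-group ordinal model (proportional odds, or rank ANCOVA) containing arm, sex, age, MMSE and B-ADL. Baseline NPI total may be added as an optional, pre-specified covariate for power.
- **Secondary interval outcomes measured at T0 and T1.** Use ANCOVA on the T1 value with arm, the T0 value and the four factors, in place of pre-post analysis of variance. The two sensor episodes during the intervention (Fig. 2) fall outside a T0/T1 model and need their own statement.

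The minimisation factors are already recorded, and T0 values follow from the pre-post design, so no new data are needed. The cost is a change of wording, a few degrees of freedom (four for the factors, one more for each baseline score), and a check of the proportional-odds assumption if that model is used.

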## Discussion

The treatment of BPSD is challenging as patients with dementia are prone to suffer from severe side effects of pharmacotherapy [47]. Furthermore, psychopharmacotherapy often has no significant effects on BPSD or may even worsen behavioural symptoms in the patients [48]. Therefore, non-pharmacological approaches for the treatment of BPSD are essential. Establishing non-pharmacological treatment and especially physical activation therefore represent a fruitful and promising approach [5]. Hence, we plan to implement a hospital-based day-structuring exercise programme for demented patients suffering from exacerbated behavioural symptoms.

To our knowledge, this is the first randomised controlled trial in inpatient hospital dementia care investigating the effects of multiple exercise sessions in the course of a day. Whereas former intervention trials and routine inpatient dementia care provide exercise sessions in a rigid time schedule for approximately one hour per session [14], this trial offers four flexible short-time exercise sessions throughout a day. In a hospital setting, ward routines and intra-daily variations of the patients’ mood or behaviour are most reasons for non-participation in exercise sessions. If a patient has no motivation to take part in an exercise session, or is hindered due to nursing or medical routines, there is in most cases no further chance to take part in guided physical activation throughout the same day. In order to circumvent these problems, the *exercise-carrousel* schedule offers multiple low-threshold exercise sessions during a day. From our clinical experience, this exercise programme should increase the patients’ willingness for participation. Therefore, we expect a better exercise-adherence compared to routine care and former trials focussing on physical activation in dementia [14]. In accordance with Christofoletti *et al.* [6], this programme represents an innovative strategy to increase exercise-adherence in dementia patients, thereby possibly leading to decreased BPSD.

Additionally, we are also interested in the influences on circadian rhythm disturbances. Disrupted circadian motor behaviour is often seen in demented patients; that is, fragmentation of rest-activity cycles or wandering-phenomenon. Actually, there are recommendations to perform exercise sessions in the morning hours [49]. As behavioural disturbances more often occur in the afternoon and evening hours, Rimmer and Smith [49] were more concerned with behavioural disturbances that may intervene with exercise sessions at that time. In most hospital and nursing home settings, physical and occupational therapy is therefore centred in the morning hours. Consequently, in daily routines for dementia patients there is often a lack of guided activities in the afternoon and evening hours. National guidelines and international expert panels demand the provision of day structure as non-pharmacological treatment of circadian rhythm disruptions [15, 50, 51]. To our knowledge, no trial focussing on the provision of day structure through physical activation in dementia care has been conducted so far [15, 51].

We plan a trial that provides structured rest- and activity-sequences in the course of a day and investigates the synchronising effects on circadian rhythm disturbances. Intervention days are planned on three non-consecutive days a week in addition to usual care with daily co-therapies, nursing and medical applications. To our knowledge there is no evidence, and neither are there recommendations, for daily structured activities as treatment of circadian rhythm disturbances. Within the thrice weekly exercise schedule, we expect a day of rest to be necessary for the patients and for the evaluation of exercise effects on circadian disruptions on intervention and non-intervention-days. Based on the experiences from our pilot project, a day of rest between the intervention days seems to be useful for these older population patients.

In order to appropriately assess behavioural symptoms, circadian rhythm disruptions and the effects of the day-structuring exercise schedule, we suggest an innovative combination of body-fixed motion sensors, well-established instruments for the rating of BPSD (NPI, CMAI) and physiological parameters (saliva-cortisol, BDNF). The upcoming complementary use of hybrid motion sensors is an especially important methodological advancement evaluating the association between disrupted motor activity and behavioural symptoms in dementia [46]. Wrist-worn accelerometers, logging and analysing the periodicity of limb movements on the basis of activity counts, are usually used to investigate movement behaviour and circadian rhythm disruptions [52]. Sensors logging the periodicity of body postures, may be superior to activity counts in analysing these symptoms. The results of our planned trial may help to implement and improve the clinical use of body-fixed sensors in assessing circadian and behavioural symptoms in patients suffering from dementia [46, 53].

Considering the methodological issues, a major challenge in conducting clinical trials is to prevent selection bias and achieve allocation concealment for all investigators throughout the whole trial. Therefore, all investigators involved in the assessment of patients (BPSD, motor behaviour, cortisol, BDNF) and the staff of the ward are blinded to group allocation. Trial design as well as the definition and recording of intervention adherence are important features when conducting exercise trials in patients with dementia. In accordance to Edwards *et al.* [44], we will rate exercise adherence regarding time, intensity and degree of exercise performance. We do not plan to use standardised self-reported rating scales to assess exercise exertion (for example, via Borg score [54]), as these scores are not reliable in patients with advanced dementia [55]. Apart from the application of body-fixed motion sensors, which provide reliable and objective information about motor behaviour during participation in exercise sessions, there is no further monitoring of exercise exertion planned for this trial. On the one hand, the monitoring of heart rate and blood pressure during exercise participation has not been feasible during the pilot project. These patients were often distracted and sometimes refused to wear the monitoring devices. On the other hand, we experienced small motor sensors fixed on the lower back to be out of the patients’ focus and therefore to be well accepted. The lack of instrumental monitoring of exercise exertion represents a limitation of this trial. Because this pragmatic method favours the provision of best possible low-threshold exercise participation, with the lowest possible obstruction before and during an exercise session, this approach has possible methodological limitations, but it is also a simple, transferable approach for routine care. Furthermore, the 2-week intervention phase only allows investigation into the short-term effects of the exercise programme. Taking into account the regular stay length of 4 to 5 weeks in inpatient old age psychiatric hospital care, the design of this trial schedules a 2-week intervention phase, due to 1 week after admission for familiarisation with the setting and delirium exclusion, and 3 days for pre- and post-assessment, respectively. Apart from the usually recommended long-term exercise schedules, the investigation of an intensive short-term *exercise-carrousel* programme represents, from our point of view, an appropriate and easily transferable approach at this stage of care. Obviously, this intensive exercise intervention programme requires a greater use of therapy resources and may negatively interact with other hospital routines.

Physical activation is a key part of non-pharmacological treatment, but despite the clinicians’ advice to apply non-pharmacological methods for the treatment of BPSD [4], there are no recommendations and guidelines for inpatient hospital dementia care. The results of our study may help to increase the evidence in the field of exercise science and non-pharmacological treatment. The *exercise-carrousel* approach can further advance non-pharmacological treatment, leading to potential worthwhile developments for patients, medical staff and caregivers in dementia care.

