## Methods/Design

### Design

An RCT with pre- and post-intervention-assessment (Fig. 1) will be conducted in the department of old age psychiatry at the LVR-Hospital Cologne, an academic teaching hospital of the University of Cologne. All assessors of eligibility criteria and outcome measurements will be blinded to group allocation. Ethical approval was obtained by the Ethics Commission of the German Sport University Cologne and the Ethics Commission of the North-Rhine Medical Chamber (reference number: 2014216). This trial is registered in the German National Register of Clinical Trials (DRKS00006740).

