#### Outcome measures

All outcome measurements will be conducted by experienced assessors from nursing and medical staff, blinded to group allocation. Primary and secondary outcome variables are presented in Table 1.

**Table 1 Tab1:** Objectives and instrumental set-up of the trial

	Variable	Instrument
Primary objective	Behavioural and psychological symptoms (BPSD)	Alzheimer’s Disease Cooperative Study-Clinical Global Impression of Change [33]
Secondary objective	Dimensions of BPSD	Neuropsychiatric Inventory (NPI) [35]
		Cohen-Mansfield-Agitation-Inventory [36]
	Caregiver burden	NPI-caregiver-subscale [35]
	Application of antipsychotics	Chlorpromazine-equivalents [34]
	Application of benzodiazepine	Diazepam-equivalents [36]
	Motor behaviour	Body fixed motion sensor
	Saliva cortisol levels	Demeditec™ saliva kits [42]
	Neurotrophic factor levels	Brain-derived neurotrophic factor from blood-serum probes [44]

As the overall effect of our intervention on BPSD as rated by the ADCS-CGIC [24, 25] is the primary outcome, that is the measure on which we will focus.

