Secondary outcome measures include dimensions of BPSD rated by the Neuropsychiatric Inventory (NPI) [33] and the Cohen-Mansfield-Agitation-Inventory (CMAI) [34]. All psychopathometric assessments will be accomplished by blinded investigators, who are responsible for interviewing both the caregiver as well as the medical and nursing staff. Further secondary outcome variables include the assessment of caregiver burden via the NPI-caregiver-subscale [33] and the effects on the application of two categories of psychotropic medication: antipsychotics and benzodiazepines. The individual dosage per day of routine and pro-re-nata medication will be converted for antipsychotics to Chlorpromazine equivalents [35] and for benzodiazepines to Diazepam-equivalents [36, 37]. The patients’ motor behaviour will be assessed by an inertial body-fixed sensor system. Body postures will be detected in four periods of 72 consecutive hours (see Fig. 2), based upon accelerometer, gyroscope, and magnetoscope data. As recommended by Trost *et al.* [38], the sensor system will be placed at the nearest possible position to the body centre of mass, the lower back. In accordance to Hatfield *et al.* [39], diurnal saliva cortisol-levels will be assessed every four hours from 08:00 a.m. to 12:00 p.m. on two consecutive days at T0 and T1 with Demeditec™ saliva kits (Demeditec Diagnostics GmbH, Kiel, Germany) [40]. Analysis of saliva cortisol-levels will be carried out via an enzyme-linked immunosorbent assay (ELISA). In order to analyse the effects on brain-derived neurotrophic factor (BDNF), blood-samples will be taken on the first intervention day at 08:30 a.m., at 05:00 p.m. and for T1 at 08:30 a.m. These samples will be centrifuged, blood serum will be stored in a fridge by -40 °C and the ELISA analysis will be realised via R & D Systems™ (R&D Systems Inc., Minneapolis, USA) [41–43]. Adverse events are recorded and a potential relation to the intervention will be evaluated by a senior old age psychiatrist, who is not part of the study team.

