#### Intervention

TAU includes exercise therapy for 45 minutes twice weekly. Patients within the study group will receive a 2-week exercise programme. On 3 non-consecutive days of the week, the patients allocated to the study-group will be offered four exercise sessions a day (see Table 2). In order to ease the patients’ participation, the exercise instructor will see the patient on his ward and ask him to take part in an exercise session. If the patient refuses or is hindered for other reasons, the exercise instructor will, however, see the patient at the next scheduled exercise session (Table 2) and offer him further participation. After positive feedback, a single session will be held for a net time of 20 minutes. After one exercise session, there will be a rest period of one hour. This specific time schedule will be carried out four times on each intervention day. Due to the provision of recurrent rest-activity periods throughout a day, this activation programme is called *exercise-carrousel.* The patients will be allocated to three different exercise groups with a maximum of three patients per instructor. Two exercise sessions include endurance exercise on seated-ergometers for the upper and lower limb. Furthermore, two exercise sessions focusing on strengthening exercises with wrist- and ankle-worn weights will be carried out. The net exercise time of 20 minutes includes two minutes of warm-up at the beginning and two minutes of cool down at the end. An endurance-exercise-period of 16 minutes or alternatively six strengthening exercises will be carried out.

**Table 2 Tab2:** Exercise carrousel schedule for one intervention day

Time/Group	a.m.						p.m.						
	09:00	09:30	10:00	10:30	11:00	11:30	00:00 to 02:00	02:00	02:30	03:.00	03:30	04:00	04:30
Group 1	I			II			Lunch break	III			IV		
Group 2		I			II				III			IV	
Group 3			I			II				III			IV

Strengthening sessions include six standardised strengthening exercises for the lower limb with two to five kilogramme ankle-worn weights on both legs (sit-stand, knee-extension in sitting position, standing heel-raise, knee-curl in standing position, hip-abduction and hip-extension in standing position); for the upper limb with 1- to 2-kg wrist-worn weights on both arms (biceps-curl, extended shoulder-lift in sitting position, rowing in 90° shoulder-abduction, shoulder-lift and shoulder-abduction in standing, dips on arm rest while sit-stand).

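### The statement that ward staff are blinded does not fit the way exercise patients are collected on the ward, and those staff are informants for the ratings made at T1

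*Protocol article*

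**What the plan says.** The protocol article makes four blinding statements of different reach:

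- Design: "All assessors of eligibility criteria and outcome measurements will be blinded to group allocation".
- Allocation and concealment of allocation: central randomisation is combined with "the blinding of all investigators during the whole trial, allocation concealment will be realised in the course of the trial".
- Outcome measures: "All outcome measurements will be conducted by experienced assessors from nursing and medical staff, blinded to group allocation".
- Discussion: the investigators who assess behaviour, motor behaviour, cortisol and BDNF "and the staff of the ward are blinded to group allocation".

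On delivery, the Intervention section says that "the exercise instructor will see the patient on his ward and ask him to take part in an exercise session". After a refusal the instructor comes back for the next slot. Four sessions are offered on each of three non-consecutive days a week, for two weeks. Controls are offered two one-hour table-game sessions a week.

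On measurement, the primary outcome is the ADCS-CGIC. The Outcome measures section says that blinded investigators carry out all psychopathometric assessments and are "responsible for interviewing both the caregiver as well as the medical and nursing staff".

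**The concern.** The ward-staff statement describes a property that the trial's own procedures remove. An instructor who appears on the ward at set times and takes the same patients away several times a day shows the allocation to anyone working there.

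This matters because ward staff also supply information for the outcome. A global impression of change is a judgement, and the NPI, its caregiver subscale and the CMAI depend on what informants report. An informant who knows that a patient is in the exercise programme, and expects it to help, may report more improvement. A blind rater would record that report in good faith. The error would most plausibly favour exercise. A reader who relies on the Discussion would think this route was closed.

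**Working it through.** **Step 1. How visible is the difference between arms?** Inputs are from the Intervention section.

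- Exercise arm: 4 offers a day × 3 days a week × 2 weeks = 24 offers per patient.
- Control arm: 2 sessions a week × 2 weeks = 4 sessions per patient, assuming the games run over the same two weeks (the article gives only the weekly number).
- Ratio: 24 / 4 = 6.
- Usual care adds exercise therapy twice a week in both arms. Exercise contacts per week are then 12 + 2 = 14 in the study group and 2 in the control group.

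The arms differ in activity, number and timing of contacts. The article describes nothing that hides the collection from staff.

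**Step 2. Does this reach the primary outcome?** Ward collection (Intervention) lets staff infer the arm. Medical and nursing staff are interviewed for the ratings (Outcome measures). The reference there to all psychopathometric assessments is read as including the ADCS-CGIC. On that reading, informants who probably know the arm contribute to the primary rating.

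**Step 3. Which assessments are exposed?** Allocation follows the T0 assessment (Allocation and concealment of allocation). T0 ratings are therefore not affected. T1 ratings, and change from T0 to T1, are.

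**Step 4. Illustration of the consequence.** The article gives no bias, so the bias b below (in SD units) is an assumption. The group size is the planned 53.

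Method: Wilcoxon–Mann–Whitney test with efficiency 3/π, by the noncentral t distribution.

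- Effective n = 53 × 3/π = 50.6 per group.
- Degrees of freedom = 2 × 50.6 − 2 = 99.2.
- Noncentrality = b × √(50.6/2) = 5.03 × b.

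Check against the plan: with d = 0.5 the noncentrality is 2.52. A one-sided 0.05 test then has power 0.803, and 53 is the smallest group size that reaches 0.80, so the stated figure is reproduced. A two-sided test has power 0.702 at 53. The article does not state sidedness, so both are shown.

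Probability of a significant result when the true effect is zero:

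| Assumed bias b | One-sided 0.05 | Two-sided 0.05 |
|---|---|---|
| 0.1 SD | 12.6% | 7.9% |
| 0.2 SD | 25.9% | 16.9% |
| 0.3 SD | 44.2% | 32.1% |

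These rates would hold for any trial of this size with that bias. They show sensitivity and do not estimate what will happen here.

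**The case against.** **The limitation is already disclosed.** The Abstract lists concealment throughout the trial among the key challenges and main limitations. That is a plain admission, but a general one. The Discussion then offers ward-staff blinding as the answer to the challenge, and nowhere says that informants may know the arm. The specific statement is not withdrawn.

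**An article condenses the protocol.** Where assessors are based and how they are shielded may well be in the full document. This stands for the raters. It does not rescue the ward-staff sentence, which is an affirmative claim that conflicts with another section of the same article.

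**Being taken to exercise is not unique to one arm.** Usual care includes exercise therapy in both arms, and controls have an active comparator. This tempers the point, but four visits a day remain distinctive.

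**Staff are not the only informants.** The caregiver is interviewed too. This may dilute the influence of staff but does not remove it.

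Three stronger readings are tempting and are not supported:

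- A reader might infer that the raters can see the allocation, since they come from nursing and medical staff. The article does not say that they work on the patient's own ward.
- A reader might infer that the claim of blinding for all investigators is refuted. The Discussion lists assessing investigators separately from ward staff, and visibility on the ward contradicts only the latter.
- A reader might infer that on-demand medication is given by the same unblinded staff. The article does not say who gives it.

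**Conclusion.** The ward-staff blinding statement does not hold as written. Staff can readily infer allocation from 24 ward-based offers per exercise patient against about four control sessions. As informants alongside the caregiver, they leave T1 and change ratings open to expectation bias even if every rater stays blind. This rests on two readings: that the psychopathometric assessments include the ADCS-CGIC, and that collection on the ward is not hidden by some measure the article omits.

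Unblinding of raters is possible but not shown. The size of the bias is unknown; the rates in the table depend wholly on assumed values and should carry no weight beyond illustration. It would also go too far to treat the motor-sensor data as an objective check on the primary result: they record motor behaviour and do not measure global BPSD.

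**What to change.** In the text:

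- Withdraw the statement that ward staff are blinded, or reconcile it with the Intervention section.
- Describe staff informants as probably unblinded, and limit the blinding claim to the assessors.
- State residual informant bias as a limitation of the ADCS-CGIC, NPI and CMAI results, and do not present the sensor data as validating those ratings.

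In conduct, where existing assessors allow:

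- Have T1 ADCS-CGIC, NPI and CMAI rated by an assessor from another of the three units.
- Instruct informants not to mention sessions or programme.
- Record the assessor's guess of allocation at T1, one item on a form.

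The cost is rota scheduling and a more modest blinding claim. No extra staff are needed if assessors are available across the units, which the article does not document. Recruitment has begun (Trial status), so the conduct steps would apply to patients still to be assessed; the text can be corrected at any time. These steps protect the rater. They do not blind the informants, which is why the limitation must still be stated.
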